#### Other measures

At baseline, participants complete: (i) a validated VDA [44, 45]; (ii) executive function tasks of attention and working memory via the validated University of Pennsylvania Computerized Neurocognitive battery (Penn CNB [21, 46]: specifically the Penn Continuous Performance Test, the Letter N-Back test, Penn Go/No-Go task, and the Penn Abstraction and Working Memory task); (iii) a day-of performance factors survey (sleep/restfulness, caffeine and medication intake, and mood via the Positive and Negative Affect Schedule scale [47]); (iv) two impulsive personality scales: *acting-without-thinking* from the Eysenck Personality Inventory, Impulsivity Subscale [48]; and Temporal Discounting or Delay Discounting via a standard monetary reward task for children [49] (v) a Sensation Seeking scale (4-items form of the Zuckerman’s Sensation Seeking Scale [50]); (vi) a survey of demographic and household factors (vehicle access and features, living situation and household financial status indicators); (vii) items from the adolescent health risk questionnaire (risk behaviors, relationship with parents); (vii) a driving history survey (crashes and citations). In addition, demographic data from the electronic health record will be collected: age, sex, child opportunity index (COI) scores as neighborhood measures of financial status and opportunity [51]. 

During the intervention phase (i.e., learner permit to licensure), participants will receive monthly surveys to ask about their learning to drive (via the driving practice quality questionnaire [52]) and crashes and citations. Participants’ driving exposure (a confounder) will also be passively monitored via the Way to Drive app. This also has an algorithm that predicts likely crash events, which will be analyzed retrospectively as an exploratory outcome. Intervention adherence will also be tracked (via driving instructor progress reports and online e-learning platform data for online intervention progress and completion).

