### Sample size

The target sample size for this randomized controlled trial is 1000 evaluable participants, with approximately 333 in each study arm (one group may include 334). This is based on the primary hypothesis of a reduction in hard braking events with driver training. The trial is powered to detect a 20% reduction in hard-braking events, a threshold identified by the U.S. Department of Transportation as predictive of reduced crash risk [57]. Additionally, it is designed to detect differences in state licensure exam pass rates between groups ranging from 15 to 19%, as well as an absolute increase of 10% to 13% in the proportion of drivers assigned to safer skill categories based on VDA classification. These thresholds reflect meaningful improvements in driving safety. A priori power analysis accounted for up to 20% attrition while maintaining 80% power to detect clinically meaningful effects, resulting in a worst-case scenario of 266 participants per arm. Retention strategies and participant replacement procedures are expected to mitigate attrition, leading to a final sample size of n = 800–1,000.

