### Allocation

After enrollment and baseline assessments, trial participants will be randomized into one of three cohorts in a 1:1:1 ratio so that there will be approximately 333 subjects in each arm, stratified by equal-size age categories (16 and 17) per arm. Randomization will be automatically conducted via the OnCore Clinical Trial Management System (CTMS). Allocation will be made by randomly generating block sizes of 6 and assigning individuals within an age category using the block assignments as they become available for randomization; this will be repeated until all individuals within an age group have been assigned to one of the three intervention arms.

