### Statistical methods

Primary and secondary outcomes will be analyzed by intention-to-treat, with each outcome assessed with a separate model. Results will be interpreted based on both statistical significance (α = 0.05) and effect size, emphasizing clinically meaningful differences. As a secondary analysis, baseline covariates will be included in the model, including age at enrollment, sex, and initial VDA class. Additional factors will be examined as potential confounders (e.g., time between first VDA and licensure) and mediators (e.g., number of practice trips, miles driven, and self-reported practice quality).

To address any non-compliance in the intervention, we will use instrumental variable (IV) analysis [58], which treats the randomization assignment as the instrument. We will also consider principal stratification [59], which can relax some of the assumptions about instrumental variable analysis such as no effect of intervention assignment independent of intervention. Both of these methods attempt to estimate intervention effects among young drivers who would comply with intervention assignment regardless of assigned intervention arm. Compliance will be defined as completing more than 2/3 of the training; in the BTW arm, this would entail completing two of the three lessons. In the ACCEL and active control arms, this would entail completion of at least 2/3 of the content. In follow-up analyses, we will include the proportion of training received as a continuous measure, operationalized as the percentage of lessons completed in the assigned intervention, and utilize the mediation analyses, treating training received as a form of mediation. In all analyses we will consider log or power transformations to reduce skewness in the outcome.

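### The primary models leave out the age stratum used in randomisation and the baseline driving-skill class, at some cost in precision but not in validity

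*Protocol article*

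**What the plan says.** Under Allocation, participants are "randomized into one of three cohorts in a 1:1:1 ratio", "stratified by equal-size age categories (16 and 17) per arm". The method is blocked within stratum: "Allocation will be made by randomly generating block sizes of 6 and assigning individuals within an age category".

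Under Other measures, "At baseline, participants complete: (i) a validated VDA". The Allocation and Blinding sections both place baseline procedures before assignment, so VDA class is a true pre-randomisation covariate.

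Under Statistical methods, "Primary and secondary outcomes will be analyzed by intention-to-treat, with each outcome assessed with a separate model". The next step on covariates is: "As a secondary analysis, baseline covariates will be included in the model, including age at enrollment, sex, and initial VDA class". No section places the age stratum, sex or VDA class in a primary model.

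Under Sample size, the power analysis "accounted for up to 20% attrition while maintaining 80% power to detect clinically meaningful effects", with a worst case of 266 per arm. The significance level appears in "statistical significance (α = 0.05) and effect size"; sidedness is not stated.

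**The concern.** Blocking within age category forces the arms to be balanced on age. That balance removes the age contribution from the sampling variability of the treatment difference. A model without an age term still counts the between-stratum variance as error, so its standard error is larger than the design warrants.

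Initial VDA class raises a related issue. It is a direct measure of the skill that training is meant to change. The Introduction attributes most crashes to driver error arising from lack of skill and experience, and Aim 3 looks for age-related risk factors. On the trial's own reasoning, both variables should carry some prognostic information. Leaving them out of the primary model gives up that information on the two outcomes that decide the trial.

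What is at stake is the width of the intervals and the power of the primary tests.

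**Working it through.** **Inputs from the article.** 333 per arm; 20% attrition; 266 per arm in the worst case; 80% power; α = 0.05, taken here as two-sided.

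**The plan's own figure.** 333 × 0.8 = 266.4, so 266 per arm is reproduced. The 80% power cannot be reproduced, because no control rate, standard deviation or dispersion for hard braking is given. It is taken as stated.

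**Assumption.** R², the share of outcome variance explained by age stratum, sex and initial VDA class, is not given. A range of 1% to 15% is used. The lower end matters because the strata are adjacent years of age and VDA class may predict hard braking only weakly.

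**Power with adjustment at 266 per arm.** With unadjusted power of 80%, the standardised effect is 1.960 + 0.842 = 2.802. Adjustment divides the standard error by 1/√(1 − R²), so

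power = Φ(2.802/√(1 − R²) − 1.960).

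**Power at 333 per arm.** The standardised effect becomes 2.802 × √(333/266) = 3.135, and unadjusted power is Φ(3.135 − 1.960) = 88.0%.

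| R² | Power, 266 per arm | Power, 333 per arm | n per arm matching unadjusted 266, 266 × (1 − R²) |
|---|---|---|---|
| 0 | 80.0% | 88.0% | 266 |
| 0.01 | 80.4% | 88.3% | 263 |
| 0.05 | 82.0% | 89.5% | 253 |
| 0.10 | 84.0% | 91.1% | 239 |
| 0.15 | 86.0% | 92.5% | 226 |

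The gain is 0.4 to 6.0 points at 266 per arm and 0.3 to 4.5 points at 333.

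**Conservatism from ignoring the stratum.** If age alone explains R²(age) and is balanced by design, the true level of a nominal 0.05 test is 2 × [1 − Φ(1.960/√(1 − R²(age)))]:

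- R²(age) = 0.01: 0.049
- R²(age) = 0.05: 0.044
- R²(age) = 0.10: 0.039
- R²(age) = 0.20, shown as an extreme: 0.028

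A simulation with 266 per arm, two equal strata and 10,000 trials per setting agrees in direction. Monte Carlo standard error is √(0.05 × 0.95/10,000) ≈ 0.002. At R²(age) = 0.20, type I error was 0.030 unadjusted and 0.051 adjusted, and power was 0.830 and 0.882. At 0.05, type I error was 0.044 and 0.051. At 0.10 the unadjusted value was 0.044, above the formula's 0.039, in a run where the adjusted test also came out high at 0.0545. At 0.01 the two tests could not be told apart (0.052 and 0.053).

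**Refinement.** Because stratification already balances age, the unadjusted test does slightly better than its nominal power: Φ(0.842/√(1 − R²(age))) is 80.1% at 0.01 and 80.6% at 0.05. To the extent that R² comes from age rather than from VDA class or sex, the gains in the table are therefore slightly overstated.

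**Limits of the formula.** It is for a continuous or log-transformed outcome with independent observations, and is only approximate for the binary pass rate. The Trial design section describes an individually randomised group-treatment design with clustering by instructor in the behind-the-wheel arm. Individual-level covariates mainly reduce variance between individuals, so the gain in contrasts with that arm may be smaller than shown.

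**The case against.** The strongest reply is that a simple intention-to-treat comparison with a prespecified adjusted analysis behind it is a respectable choice, and that a condensed article leaves full model specification to an analysis plan that is not shown. The article never uses the word unadjusted, and age at enrollment as a covariate is not the same thing as a 16/17 stratum term. Part of this stands: the absence of the stratum from the primary model is inferred from the contrast between primary and secondary analyses, not stated outright. But the article does more than stay silent. It assigns age, sex and VDA class to a secondary analysis, and a primary model that already contained them would make that sentence pointless.

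It is also fair that the effect nearly vanishes if R² is about 1%, and that 266 per arm is the floor and not the target. Both are reflected in the table.

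Four stronger readings are tempting, and the documents do not support them:

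- A reader might infer that the primary result would be biased or its type I error inflated. Randomisation protects the unadjusted comparison, and ignoring the stratum errs towards caution.
- A reader might infer that two models leave two competing answers per outcome. The article ranks them, so the primary answer is clear.
- A reader might cite larger gains for the VDA at licensure. That is a secondary outcome in Table 1, and the listed change score already uses the baseline VDA.
- A reader might want baseline practice hours in the model, since eligibility caps them below 30. The cap is an eligibility threshold; hours are not listed among the baseline measures, and in Table 2 the practice questionnaire starts after allocation.

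**Conclusion.** The point holds as a matter of efficiency. The primary analysis as described does not reflect the stratified design and sets aside a baseline skill measure already in hand. The cost is a somewhat conservative test and wider intervals than the data allow. Under an assumed R² of 1% to 15% for a continuous or log-transformed hard-braking outcome, the power given up is about 0.4 to 6 points at 266 per arm and 0.3 to 4.5 points at 333, possibly less in behind-the-wheel contrasts. The size rests wholly on that assumed R². The direction does not: for such an outcome, adjustment for prespecified prognostic baseline covariates is not expected to lose meaningful precision at this sample size. The change is worth making because it is nearly free. The validity of the trial does not depend on it.

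**What to change.** Make the primary models for hard braking and for first-attempt pass include the randomisation age stratum (16/17), sex and initial VDA class. Keep the unadjusted model as a named sensitivity analysis.

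For the pass rate, report a standardised (marginal) risk difference from the adjusted logistic model. The conditional odds ratio from that model is a different quantity from the unadjusted one even under perfect balance, whereas the risk difference matches the percentage-point target under Sample size.

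Do not add baseline practice hours unless it is confirmed that they are recorded before randomisation.

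The cost is wording in the analysis plan. The three covariates are already named by the article as model covariates. Data collection is ongoing and no interim analyses are planned, so the order can be switched, and the switch dated, before any comparison by arm has been seen.

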**Fig. 1 Fig1:**
[figure not shown]
Flow diagram of participant progression through the trial, with participation estimated between 8–18 months (with varying learner/intervention phase)

**Table 2 Tab2:** Outline of the schedule of enrollment, interventions, and assessments

Timepoint	Enrollment	Baseline	Allocation	Intervention						Post-intervention	Post-Licensure		
	*-t*_*1*_	*t*_*1*_	*0*	*m*_*1*_	*m*_*2*_	*m*_*3*_	*m*_*4*_	*m*_*5*_	*m*_*6*_	*t*_*2*_	*m*_*8*_	*m*_*10*_	*m*_*12*_
Enrollment:	*X*												
Eligibility Screen	X												
Informed Consent/Assent	X												
Allocation to Trial Arm			X										
Interventions:													
Active Control Online Education				X	X	X	X	X	X				
ACCEL Online Driver Skills Training				X	X	X	X	X	X				
Behind-the-Wheel Training				X	X	X	X	X	X				
Assessments:													
Virtual Driving Assessment		X								X			
Penn Neurocognitive Battery		X											
Day-of-Performance Factors		X											
Driving Intake (status)		X											
Driving History (crashes/citations)		X		X	X	X	X	X	X	X	X	X	X
Personality Scales		X											
Demographic & Household Factors		X								X			
Adolescent Health Risk Factors		X											
Way to Drive Monitoring													
Driving Practice Quality Questionnaire				X	X	X	X	X	X	X			
Hazard Skills Test										X			
State Licensing Examination										X			
Driver Behavior Surveys										X	X	X	X

This table outlines the schedule of study procedures and provides an approximate length of participation, however, the intervention phase length will vary, and some drivers may need to retake the state license examination, extending the time before post-licensure follow-up. T1 and T2 = study assessment timepoints before and after the intervention learner permit phase; m = month

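### Time to licensure and learner-phase driving exposure are called confounders although both arise after randomisation; adjusting for them can bias the training effect in the additional models

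*Protocol article*

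**What the plan says.** All references are to the protocol article.

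- **Main analysis (Statistical methods):** "Primary and secondary outcomes will be analyzed by intention-to-treat, with each outcome assessed with a separate model".
- **Adjusted analysis (same section):** "As a secondary analysis, baseline covariates will be included in the model, including age at enrollment, sex, and initial VDA class". All three named covariates are known before allocation.
- **Next sentence (same section):** "Additional factors will be examined as potential confounders (e.g., time between first VDA and licensure". The same sentence goes on to name "mediators (e.g., number of practice trips, miles driven, and self-reported practice quality".
- **Other measures:** "driving exposure (a confounder) will also be passively monitored via the Way to Drive app". The paragraph holding this remark opens with "During the intervention phase (i.e., learner permit to licensure), participants will receive monthly surveys", so the exposure meant is that of the learner phase.
- **Timing (Allocation):** "After enrollment and baseline assessments, trial participants will be randomized into one of three cohorts in a 1:1:1 ratio". Table 2 places the first VDA at baseline, before allocation.
- **Note to Table 2:** "the intervention phase length will vary, and some drivers may need to retake the state license examination, extending the time before post-licensure follow-up".

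**The concern.** A confounder of the arm comparison has to be a cause, or share a cause, of arm assignment. Here assignment is random, so nothing that happens later can play that part. A later variable that training can change is a mediator, a consequence of the outcome, or a variable that shares unmeasured causes with the outcome. Adjusting for it can remove part of the training effect or bring in bias that randomisation had excluded.

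The document itself gives a route from arm to time to licensure. The Objectives expect BTW to do better on the state examination, and the note to Table 2 says that retakes lengthen the time before post-licensure follow-up. For the Aim 2 primary outcome, first-attempt pass, the interval is in part a result of the outcome.

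Exposure also carries two labels that lead to opposite handling. A confounder is adjusted for; a mediator is left out of a model for the total effect. The stated objective is the protection that training adds beyond GDL, which is a total effect. The Introduction faults earlier studies for not accounting for exposure, so an estimate presented as adjusted for exposure as a confounder could be given more weight than it deserves.

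**Working it through.** The plan gives no figure on this point, so there is none to reproduce. The check has three parts.

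**1. Order of events.** Baseline including first VDA → randomisation → training and learner practice → first exam attempt → possible retake → licensure → post-licensure driving. Time from first VDA to licensure ends after randomisation. Learner-phase exposure accrues wholly after it. Age at enrolment, sex and initial VDA class are fixed before it.

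**2. Hard-braking rate.**

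From the document: a 20% reduction (Sample size), taken as a true total rate ratio of 0.80.

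Assumed, since the document gives no such values:
- training shifts the post-randomisation variable M by a = 0, −0.2 or −0.5 SD;
- M changes the log rate by g = 0 or 0.2 per SD;
- an unmeasured trait affects both M and the log rate with coefficient u = 0 or 0.4.

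Model: M = aA + uU + error, with within-arm variance 1; log rate = (ln 0.80 − ag)A + gM + uU + error. Without M in the regression, the coefficient of A is ln 0.80. With M in it, the mean of U given A and M is u(M − aA), so the coefficient of A becomes ln 0.80 − ag − au². The adjusted rate ratio is therefore 0.80 × exp(−ag − au²).

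| a | g | u | −ag − au² | Adjusted rate ratio |
|---|---|---|---|---|
| 0 | any | any | 0 | 0.800 |
| −0.2 or −0.5 | 0 | 0 | 0 | 0.800 |
| −0.2 | 0 | 0.4 | 0.032 | 0.826 |
| −0.2 | 0.2 | 0 | 0.040 | 0.833 |
| −0.2 | 0.2 | 0.4 | 0.072 | 0.860 |
| −0.5 | 0 | 0.4 | 0.080 | 0.867 |
| −0.5 | 0.2 | 0 | 0.100 | 0.884 |
| −0.5 | 0.2 | 0.4 | 0.180 | 0.958 |

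A simulation of 2,000,000 participants per scenario agreed within 0.002, and its unadjusted estimate stayed at 0.80 to within 0.001. With other signs the bias reverses: a = +0.2, g = 0.2, u = 0 gives 0.80 × exp(−0.040) = 0.769.

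**3. First-attempt pass.**

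From the document: a 15-point difference, the lower end of the 15 to 19% range in Sample size.

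Assumed:
- pass rates of 60% and 75%;
- a failed first attempt adds d = 1 or 2 months to the interval;
- other variation in the interval has SD s = 1 or 3 months and is unrelated to the result;
- everyone is eventually licensed.

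The average within-arm variance of pass is v = (0.60 × 0.40 + 0.75 × 0.25)/2 = 0.21375. Linear adjustment for the interval turns the difference into 0.15 × s²/(d²v + s²).

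| d | s | Calculation | Adjusted difference |
|---|---|---|---|
| 1 | 3 | 0.15 × 9/9.21375 | 14.7 points |
| 2 | 3 | 0.15 × 9/9.855 | 13.7 points |
| 1 | 1 | 0.15 × 1/1.21375 | 12.4 points |
| 2 | 1 | 0.15 × 1/1.855 | 8.1 points |

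Here the interval has no influence on passing at all. The shrinkage arises only because failing lengthens it.

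**The case against.** The strongest reply is that the main result is safe. Outcomes are analysed by intention-to-treat, and adjustment is a secondary analysis whose named covariates are all baseline variables. The extra factors are only to be examined; no model, outcome or decision rule is attached to them. All of that stands. A reader might infer that the primary estimate is biased or that the trial's power drops below 80%. The document supports neither: it does not put these factors in the primary model, and any power loss could be computed only by assuming how much of the effect runs through them, for an analysis that is not the primary test.

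A second reply is that bias is conditional. This also stands: if training does not shift the variable, the adjusted and unadjusted estimates agree.

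A third is that a variable can mediate the arm effect and yet confound some other relation, such as mediator with outcome, or a non-randomised trait with outcome under Aim 3. The Other measures remark sits in a list of measurements, and miles driven is not tied to a phase in Statistical methods. This is possible, but the text does not say so. Miles driven stands there between practice trips and practice quality, and the confounder sentence directly follows the adjusted model for the arm effect.

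A fourth is that a condensed article leaves model detail to a fuller document. That would excuse silence. It does not excuse a stated role that is wrong for a randomised comparison, or two sections that disagree.

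**Conclusion.** The point holds as a should-fix. The protocol labels two post-randomisation variables as confounders, and it gives exposure the opposite role elsewhere. Adjusting for either can bias the total training effect in the additional adjusted models, and for first-attempt pass the interval is partly a consequence of the outcome.

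The sizes (0.80 moving to as much as 0.96; 15 points shrinking to between 8.1 and 14.7) illustrate the mechanism and rest wholly on the assumed inputs. Bias requires that arm is associated with the variable, through training or through the exam result. For hard braking it also requires that the variable affects the outcome or shares an unmeasured cause with it. The direction for hard braking is not fixed.

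The primary intention-to-treat analysis is not shown to be affected, and no loss of the stated 80% power is claimed. Miles as the denominator of the hard-braking rate belong to the outcome definition and are not part of this point.

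**What to change.** 1. In Statistical methods, remove time from first VDA to licensure as a potential confounder. In Other measures, remove the confounder label from driving exposure.
2. State that models of the arm effect adjust only for variables fixed before randomisation, such as age at enrolment, sex and initial VDA class.
3. Report time to licensure, practice trips and learner-phase miles by arm, or analyse them as candidate mediators with the assumptions stated. If any is meant as a confounder of a different, non-randomised relation, name that relation.
4. Use post-licensure miles only as the denominator of the hard-braking rate.

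The cost is wording in two sections. Data collection, sample size and procedures do not change. Enrolment began in August 2024, primary completion is expected in December 2027 and no interim analysis is planned, so the edit can be made before outcomes are analysed.

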### Objectives

The primary objective of the DRIVER (DRIVer Education Research) study is to quantify the extent to which modern online driver training and BTW prior to licensure can add protection beyond GDL against crash risk early in licensure. The secondary objective is to quantify the effect of driver training on skill acquisition. The study aims and outcomes are summarized in Table 1. We hypothesize that both ACCEL and BTW training will reduce crash risk and improve driving skills compared to the control group. More specifically, we hypothesize that ACCEL will show greater improvement in crash risk and skills than BTW on the theory that ACCEL is more targeted to the critical reasons for crashes among novice adolescent drivers. However, we expect BTW to perform better on PA license examination outcomes since this test measures skills directly trained by BTW. We also hypothesize that those with weakness in cognitive and attentional control will benefit most from the training interventions in the key outcomes, and those with personality differences and risky driving practices linked to crash risk may be more resistant to the effects of driver training.

**Table 1 Tab1:** Summary of study aims and associated outcomes

Study Aim	Primary Outcome	Secondary Outcome
**Aim 1**. Determine the effect of driver training (ACCEL or BTW) compared to GDL alone on post-licensure crash risk	Hard Braking Events per 100 miles driven via Way to Drive monitoring app	• Phone Use while Driving (minutes per hour of driving) • Speeding (proportion of time > 10 miles over posted speed limit) • Self-reported crash involvement • Self-reported risky driving behavior
**Aim 2**. Determine the effect of driver training (ACCEL or BTW) compared to GDL alone on skill acquisition	Pass rate on the first attempt at the state licensing examination	• Virtual Driving Assessment (VDA) Performance at T2 • Change in T1-T2 VDA performance • Number of license exam attempts
**Aim 3**. Identify age-related risk factors for crashes that may moderate the response to training	Interactions with Aim 1 & 2 outcomes	Interactions with Aim 1 & 2 outcomes

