### Trial design

This trial uses random assignment with three parallel groups and follows an individually randomized group-treatment (IRGT) design. Participants are enrolled early in their learner permit and followed through licensure, and up to 6 months post-licensure, with the primary end point of crash risk at 2 months post-licensure. Participation length will vary with permit duration (range 8 to 18 months). After baseline, participants are randomized 1:1:1 to one of three groups (n = 333 per group): (i) professional BTW; (ii) ACCEL, a modern online driving skills training program; (iii) an active control online program covering vehicle safety topics without skills training. Participants in the BTW group will be clustered by instructor to account for variation in driver teaching style. Participants will be monitored remotely through the learner and post-licensure phases using surveys and a smartphone application capturing driving kinematics to quantify exposure and crash risk. At licensure, driving skill will be measured using three methods: the virtual driving assessment (VDA), an online hazard skills test, and results from the license examination. The primary endpoint is on-road kinematic crash risk (the rate of hard braking events) at 2 months post-licensure, with continued follow-up through 6 months post-licensure. Kinematic risky driving (KRD) events such as hard-braking events, have previously been validated as behavioral proxies for elevated crash risk [37–42]. See Fig. 1 and Table 2 for participant flow through the study and all procedures and measures through the trial.

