### Intervention descriptions

All trial participants will receive care as usual, including information to access a Parents Supervised Driving Program from the Pennsylvania Department of Transportation (PennDoT), as well as information on how to access the PennDoT recommended smartphone app for logging practice hours (RoadReady App). In addition, one group will receive professional BTW with a local driving school instructor (6 h: 4 × 1.5 h lessons), another group will receive ACCEL online hazard skills training (~ 2 h), and another will receive an online active control vehicle and driver safety program (~ 2 h, with no skill training). While the ACCEL intervention is shorter than BTW instruction, this program is designed to be highly interactive and cognitively engaging, focusing specifically on the skill deficits that cause young driver crashes, and thus potentially offsetting the shorter duration. While the online programs can be completed in one sitting, participants can also take breaks and resume where they left off. Adherence (progress and duration) will be tracked via the e-learning platform (ScormCloud) event log and via a quiz and test at the end of the training. For BTW, driving instructors will fill out a brief post-lesson survey to confirm lesson content covered and completion.

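### The plan says IV targets drivers who would comply in any arm; in this three-arm trial it gives a separate complier group per active arm, comparable only under an added assumption

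*Protocol article*

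**What the plan says.** The trial has three parallel arms (Trial design): "participants are randomized 1:1:1 to one of three groups (n = 333 per group"). The analysis of all primary and secondary outcomes is by intention to treat (Statistical methods). For non-compliance the same section commits to a first method, "we will use instrumental variable (IV) analysis [58], which treats the randomization assignment as the instrument", and holds a second in reserve: "We will also consider principal stratification [59], which can relax some of the assumptions about instrumental variable analysis". One sentence then gives both methods the same target population: "Both of these methods attempt to estimate intervention effects among young drivers who would comply with intervention assignment regardless of assigned intervention arm".

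Compliance is defined arm by arm. For BTW: "Compliance will be defined as completing more than 2/3 of the training; in the BTW arm, this would entail completing two of the three lessons". For the two online courses: "In the ACCEL and active control arms, this would entail completion of at least 2/3 of the content". Taken with these definitions, the stated population is drivers who would complete BTW if assigned BTW, ACCEL if assigned ACCEL, and the control course if assigned control.

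The Objectives also state an ordering of the two trainings: "we hypothesize that ACCEL will show greater improvement in crash risk and skills than BTW".

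**The concern.** The sentence carries a familiar two-arm description of compliers into a trial where each arm has its own course and its own completion rule. IV does not pick out the joint group here. Each active arm against control has its own complier group.

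The document gives reason to expect these groups to differ. BTW is "professional BTW with a local driving school instructor (6 h: 4 × 1.5 h lessons"), while ACCEL takes about 2 h online. The Introduction says cost and location make access to BTW uneven, and that online delivery removes travel.

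What is at stake is interpretation. A reader who trusts the label would take the ACCEL and BTW complier effects as describing the same drivers. A difference between them could then be read as a difference between trainings when part or all of it reflects who finishes which course.

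**Working it through.** No figure in the plan is disputed, and there is none to reproduce: the protocol gives no completion rate and no complier effect. The check is therefore on the estimand, followed by illustrations with assumed values.

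**Step 1: the stated group.** Let C_A, C_B and C_0 equal 1 if a driver would complete ACCEL, BTW or the control course when assigned to it. The label describes drivers with C_A = C_B = C_0 = 1.

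**Step 2: what IV gives.** Assume (a) nobody receives a study training outside their arm, and (b) assignment affects outcome only through completing the training. Drivers who would not complete ACCEL then contribute no difference between the ACCEL and control arms, so:

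- ITT(ACCEL − control) = P(C_A = 1) × mean effect of ACCEL among C_A = 1
- ITT(BTW − control) = P(C_B = 1) × mean effect of BTW among C_B = 1

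IV divides each difference by its own completion rate. The results are the effect among C_A = 1 and the effect among C_B = 1. C_0 appears in neither.

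**Step 3: if (a) fails for BTW.** The protocol records other ways participants learned to drive (Other measures). If outside professional lessons count as BTW received, the BTW complier group becomes drivers who would take BTW if assigned it and not otherwise.

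**Step 4: overlap of the groups (completion rates assumed).** The share of drivers with C_A = C_B = 1 lies between max(0, c_A + c_B − 1) and min(c_A, c_B).

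| c_A / c_B | Joint share | As share of ACCEL compliers | As share of BTW compliers |
|---|---|---|---|
| 95% / 90% | 85–90% | 89–95% | 94–100% |
| 90% / 70% | 60–70% | 67–78% | 86–100% |
| 80% / 60% | 40–60% | 50–75% | 67–100% |

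The mismatch shrinks as completion approaches 100% in both arms.

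**Step 5: effect on the estimates (all values assumed).** Take completion of 85% for ACCEL and 65% for BTW, with every BTW complier also an ACCEL complier. ACCEL-only compliers are then 0.85 − 0.65 = 0.20 of drivers, and 0.20/0.85 = 23.5% of the ACCEL group. Let both trainings cut the rate by 20% in shared compliers (log-rate effect ln 0.80 = −0.223), and let e be the log-rate effect of ACCEL in ACCEL-only compliers. Averaging on the log scale:

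IV(ACCEL) = (0.65 × (−0.223) + 0.20 × e) / 0.85, and IV(BTW) = −0.223, a 20.0% reduction.

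| e | IV(ACCEL) | Reduction, ACCEL | Reduction, BTW |
|---|---|---|---|
| 0 | −0.171 | 15.7% | 20.0% |
| −0.05 | −0.182 | 16.7% | 20.0% |
| −0.15 | −0.206 | 18.6% | 20.0% |
| −0.30 | −0.241 | 21.4% | 20.0% |

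The trainings do not differ in shared compliers, yet ACCEL looks worse by up to 4.3 percentage points or better by 1.4, depending on e. At e = −0.223 the gap is zero.

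**Step 6: check by simulation.** Two-stage least squares with two completion indicators and two assignment instruments was run on 3,000,000 simulated drivers under (a) and (b). The assumed mix was 65% who would complete both, 25% ACCEL only, 5% BTW only and 5% neither. Both trainings had the same effect in any given driver: −1.0, −0.4 and −0.7 in the first three groups.

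- ACCEL, by formula: (0.65 × (−1.0) + 0.25 × (−0.4)) / 0.90 = −0.833; simulated −0.833.
- BTW, by formula: (0.65 × (−1.0) + 0.05 × (−0.7)) / 0.70 = −0.979; simulated −0.977.

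The apparent gap is about 0.15 where the gap in the joint group is 0. It vanished when effects were made homogeneous, and when the two complier groups were made to coincide.

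**The case against.** The strongest reply is that the harm is hypothetical. IV only supplements intention to treat, Table 1 frames Aims 1 and 2 as each training against licensing law alone, and the ACCEL-over-BTW hypothesis is nowhere tied to IV. This stands. A reader might infer from the label and that hypothesis that the two IV estimates will be set against each other, but no passage schedules it.

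A second reply is that the sentence is a one-line gloss in a condensed article and can be read contrast by contrast. Detail on estimands may indeed sit in a plan not shown. But the sentence states a property of IV rather than leaving it open, and the pairwise reading does not rescue it. Compliance is defined for the control course too, and even a single active-against-control IV contrast does not depend on finishing that course.

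Third, describing the groups simply as those who would complete ACCEL or BTW is itself conditional: it fails if trainings are obtained outside the assigned arm. This stands, and the fix has to say so.

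Fourth, any numerical illustration rests on invented completion rates and effects. This also stands. A reader shown only weak effects in ACCEL-only finishers might infer that BTW is favoured. The last row of the Step 5 table reverses that, and the Objectives allow either direction, expecting some drivers to benefit most and others to resist training.

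**Conclusion.** The statement is accurate as an aim for principal stratification, given added assumptions. It is wrong for IV, the method the protocol commits to. IV yields two arm-specific complier effects against control, provided there is no access to a study training outside the arm and no effect of assignment other than through completion.

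It would go too far to say the two estimates can never be compared. They describe the same drivers if the complier groups coincide, and they can be compared as training effects in that case or if effects are homogeneous. The protocol assumes neither, and its own moderation hypotheses (Objectives) argue against homogeneity.

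The size and direction of any gap cannot be fixed from the document. In the assumed example the ACCEL figure ranges from 15.7% to 21.4% against 20.0% for BTW; near-complete adherence would make the problem small. The intention-to-treat conclusions are untouched. This is a misstated estimand in a supplementary analysis, worth correcting before the outcome data are analysed.

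**What to change.** Replace the sentence on the target population with text along these lines:

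- The IV estimands are (1) ACCEL against control among drivers who would complete ACCEL if assigned it, and (2) BTW against control among drivers who would complete BTW if assigned it. Both assume no receipt of that training outside the assigned arm and no other effect of assignment on outcome.
- State whether outside professional lessons count as BTW received. If they do, estimand (2) concerns drivers who would take BTW if assigned it and not otherwise.
- Leave control-course completion out of the IV.
- Say that the two estimates concern different groups and will not be compared without a stated added assumption. Leave ACCEL against BTW to the intention-to-treat contrast.
- Reserve the group who would comply in any arm for principal stratification, with its assumptions listed.

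The BTW completion rule counts three lessons where Intervention descriptions gives four, and two of three is not more than two thirds. Those passages must be reconciled, since they define the BTW complier group.

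The core change is about two sentences and needs no new data collection. The cost is giving up any claim from the IV about ACCEL against BTW in one common complier population.
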